#### Early suspension or termination of the entire study

The trial will be suspended early or terminated for the following reasons:A serious adverse event (SAE) which is probably or definitely related to the test drug occurs or more than half of the population in any of the groups experience adverse drug reactions.The efficacy of the test drug is found to be poor or even ineffective.The protocol is flawed, or there is significant deviation from the protocol.The pharmaceutical supervisory and administrative department decides to terminate the study reasonably.The sponsor decides to terminate the trial due to management or financial problems.

### Diagnostic criteria

A diagnosis of the common cold in Western medicine is established according to *Practice of Internal Medicine* (2013, 14^th^ edition) [21]. A TCM diagnosis of CCWHS is based on the chapter common cold (wind-heat syndrome) of *Internal Medicine of TCM* [22] and *TCM syndrome and sign diagnostic criteria for common cold* [23]. The TCM diagnostic criteria for CCWHS are listed in Table 2. To be diagnosed with CCWHS, patients should have all the primary symptoms and at least three of the secondary symptoms, as well as TCM signs for the tongue and pulse.

**Table 2 Tab2:** Diagnostic criteria of common cold based on TCM

Category	Symptoms and signs
Primary symptoms	Fever, mild aversion to cold, sore throat
Secondary symptoms	Weak limbs, nasal congestion, running nose, thirst, cough
Signs for the tongue	Red tongue with thin yellow coating
Signs for the pulse	Floating and rapid pulse

*TCM* Traditional Chinese medicine

### Randomization and blinding

A total of 240 eligible participants will be randomly allocated to the high-dose group, medium-dose group, low-dose group, or placebo group in a 1:1:1:1 ratio. Randomized sequences of each center and every packed drug were generated by an independent professor at the Drug Clinical Research Center of Shanghai University of TCM, using a stratified block randomization method with 30 blocks of block size 8 based on the PROC PLAN function of the SAS 9.2 software analysis system (SAS Institute, Cary, NC, USA).

Randomization sequences will be concealed in lightproof, sealed envelopes kept by a specified project manager and the sponsor, who are not involved in the recruitment, intervention, assessment, or statistical analysis. The treatment allocation will be blinded to the participants and investigators throughout the study, and the outcome assessors and statisticians will not be involved in the participants’ screening and allocation. Each patient will receive a unique randomized number corresponding to the drug according to the group allocation. Furthermore, the intervention group type will be replaced by the letter A, B, C, or D as blind codes of allocation. The blind codes will not be disclosed until the statistical analysis is completed. An emergency envelope has been prepared for each randomized number in each center and is to be opened for treatment only in case of medical emergency which is most probably caused by the study drug.

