### Safety evaluation

Adverse events (AEs) concerning clinical symptoms and signs as well as laboratory tests will be documented. Every AE will be recorded in detail, and prompt, proper treatment will be given by researchers and therapists at each center. If a serious adverse event (SAE) presents, a decision on whether the participant needs to be withdrawn from the study will be made by the principal investigator and ethics committee. The causality and relationship between AEs/SAEs and the study drug will also be analyzed and evaluated on the basis of standard operation procedures (SOPs) of the CFDA, which define causality and relationship as clearly related, probable, possible, doubtful, and clearly not. If an SAE occurs, the investigator must record it in detail on the SAE form, and it should be reported to the principal investigator, the CFDA, ethics committee, and the sponsor within 24 hours. A statistician will analyze the frequency and proportion of AEs/SAEs. Continuous care will be available until subjects who suffer harm from the participation recover, and proper compensation will also be given.

Primary vital signs, physical examinations, and some laboratory tests will be performed both before and after treatment for safety assessment. Primary vital signs include body temperature, blood pressure, heart rate, and respiration rate. Laboratory tests include routine blood, urine, and stool analysis, liver function test (ALT, AST, alkaline phosphatase (ALP), serum total bilirubin (STB), and gamma-glutamyl transpeptidase (γ-GT)), renal function test (serum creatinine, microalbuminuria, and serum cystatin C), and electrocardiogram. Also, before treatment, subjects who are suspected to have a lower respiratory tract infection need have a chest X-ray, and female patients with the potential to become pregnant must take a urine pregnancy test.

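### The emergency envelope may be opened only on a judgement that the study drug caused the emergency, not on whether the allocation is needed to manage it

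*Protocol article*

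**What the plan says.** All of this is in the protocol article, under Methods/design.

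- **Randomization and blinding, general rule.** "The treatment allocation will be blinded to the participants and investigators throughout the study". The groups carry letter codes, and "The blind codes will not be disclosed until the statistical analysis is completed".
- **Randomization and blinding, exception.** Each randomized number has an emergency envelope at its center, "to be opened for treatment only in case of medical emergency which is most probably caused by the study drug".
- **Randomization and blinding, custody.** The sequences lie in sealed envelopes "kept by a specified project manager and the sponsor, who are not involved in the recruitment, intervention, assessment, or statistical analysis".
- **Safety evaluation.** Causality is graded on five levels: "clearly related, probable, possible, doubtful, and clearly not". When a serious adverse event (SAE) occurs, "it should be reported to the principal investigator, the CFDA, ethics committee, and the sponsor within 24 hours".
- **Early suspension or termination of the entire study.** The list opens with "The trial will be suspended early or terminated for the following reasons", and its first item begins "A serious adverse event (SAE) which is probably or definitely related to the test drug occurs".

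**The concern.** An emergency envelope exists so that a treating doctor can learn the allocation when care calls for it. The rule as written asks a different question: did the study drug most probably cause this event? The two questions can have different answers. A doctor may need the allocation precisely because the cause is unclear, for instance to rule the active product in or out. Under the stated rule that doubt is what keeps the envelope shut.

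For a participant, information that could bear on emergency care may be withheld. For the trial, centers would have to interpret an undefined threshold under time pressure and could do so inconsistently. Trial status says that recruitment is under way, so the rule is already in force.

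**Working it through.** There is no planned figure to reproduce; the check is a comparison of the passages.

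**1. Conditions for opening.** The envelope sentence sets three conditions, tied by the word *only*: a medical emergency, a most probable causal link to the study drug, and treatment as the purpose. Need for the allocation is not among them.

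**2. Who judges, and in what state.** Investigators are blind throughout, and the envelope is the only code break for care that the article describes. The causality verdict must therefore come before the allocation is known.

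**3. Does the meaning of study drug change this?** Interventions sets the study drug against placebo, which makes it the active capsule. Withdrawal criteria uses the term for what every participant takes, placebo included.
- If it means the active capsule, the investigator must blame a product before learning whether it was given.
- If it means the blinded capsules, that circularity goes, but opening still depends on causation and not on need.

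The defect in step 1 stands on either reading.

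**4. Threshold against the causality scale.**

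| Level under Safety evaluation | If *most probably* means probable or higher | If it is stricter than probable |
|---|---|---|
| Clearly related | may open | may open |
| Probable | may open | closed |
| Possible | closed | closed |
| Doubtful | closed | closed |
| Clearly not | closed | closed |

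The text does not decide between the columns. On both, an emergency rated possible or lower stays blinded whatever the need. The table counts categories; it says nothing about how often each would occur.

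**5. The three relatedness wordings.** The envelope rule uses *most probably*. The suspension rule uses *probably or definitely*. The scale has *probable* and *clearly related*. *Definitely* is easily read as *clearly related*; *most probably* has no clear counterpart.

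**6. The suspension rule.** It names a relatedness level. It does not say who assigns it, or whether that person is blind. Nor does it say that the verdict must precede disclosure.

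**7. Can the chance of a suspension triggered by a placebo patient be calculated?** The placebo share is 60/240 = 25%, which only restates the 1:1:1:1 ratio. With an assumed SAE risk p per patient, equal in all arms, the chance of at least one SAE of any kind among 60 placebo patients is 1 − (1 − p)^60:

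| Assumed p | Chance of at least one SAE on placebo |
|---|---|
| 0.1% | 5.8% |
| 0.5% | 26.0% |
| 1% | 45.3% |

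The article gives no p. Nor does it say what share of such events would be judged at least probably related, so each figure is only an upper limit on the trigger for its p. No usable probability follows.

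**The case against.** **Judging relatedness under the blind is normal.** That is true, and it is no contradiction in itself. What is unusual is making that judgement the gate to emergency unblinding.

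**A journal article condenses the full protocol.** This disposes of complaints about procedures that are merely absent. It does not dispose of a rule that the article states and closes with *only*.

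**The harm is not demonstrated.** The article names no emergency in which care would depend on the allocation, and Safety evaluation promises prompt, proper treatment of every adverse event. This limits the weight of the point. It does not show that the causality test serves the purpose the envelope is given.

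**A stronger reading is tempting.** A reader might infer that the suspension rule also demands a blinded verdict before anyone may learn the allocation, so that the trial could be stopped for a placebo event. The documents do not support this, for four reasons:
- The suspension rule is silent on blinding and on sequence.
- A project manager and the sponsor keep the sequences, and the sponsor hears of each SAE within 24 hours. It is therefore too broad to say that nobody could know, although the article states no access to the sequences for safety decisions.
- An SAE that is a medical emergency and is judged probably related would broadly meet the envelope condition as well, so the allocation could be known before a final decision.
- Suspension is offered beside termination, which leaves room for a check.

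What remains is an SAE that is not an emergency needing the code for care. For that case the article does not say whether exposure is confirmed first. This is silence, and the full protocol may fill it.

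**Conclusion.** The point holds for the envelope rule. As written, the rule bars unblinding when the allocation is needed for care but causation is uncertain or judged only possible, and its threshold is not on the trial's own causality scale. This rests on the literal wording and on neither reading of *study drug* in particular.

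It is a participant-safety and conduct point that should be corrected while recruitment continues. It affects neither the sample size nor the planned tests, and the documents give no basis for a frequency.

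On the suspension rule the conclusion is narrower: the blinding status of the relatedness judgement is unstated and should be reconciled with the envelope rule. The article does not require a blinded verdict before a suspension or termination. The 25% placebo share is not a probability of one.

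**What to change.** 1. **Randomization and blinding.** Replace the causality condition with this criterion: the envelope may be opened when knowledge of the allocation is needed to manage the medical emergency. Require each opening to be logged.
2. **Relatedness terms.** Use the levels of the Safety evaluation scale wherever relatedness is named, so that the envelope section, the suspension rule and the scale agree.
3. **Early suspension or termination.** State whether relatedness is judged blinded or unblinded, and by whom, consistently with Randomization and blinding.

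The cost is an amendment of a few sentences. The downside is perhaps a few more single-patient unblindings among 240, each 1/240 ≈ 0.4% of the sample. Opening an envelope does not by itself remove a participant from the full analysis set, which asks for at least one dose and an observation record. Diary entries made after an opening could be influenced if the participant learns the allocation, which the log would allow the analysis to identify.

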### Interventions

LJGMC and the placebo are provided and manufactured by Tasly Pharmaceutical Co., Ltd. (Tianjin, China). Each LJGMC or placebo weighs 0.28 g. The production batch number is 20150101. All the drugs are packaged uniformly with the same labels. Each package, which contains 3 plus 1 days’ dosage, must be sealed and kept in a cool, dry place. The placebo, which contains no effective ingredients to treat the common cold, is almost identical to the study drug in appearance, smell, and taste. A clearly visible label on each package states “FOR TRIAL USE ONLY” and other information: name, dose, dosing schedule, indication of storage condition, expiration date, and the manufacturer’s name. An independent drug manager in each center is in charge of receiving, handling, storing, and dispensing the drugs.

Patients in the high-dose group, medium-dose group, low-dose group, or placebo-matched group will receive, respectively, 1.12 g LJGMC, 0.56 g LJGMC plus 0.56 g placebo, 0.28 g LJGMC plus 0.84 g placebo, or 1.12 g placebo each time, three times per day. All medications will be taken orally with 200 ml warm water. The treatment duration is 3 consecutive days, with a 5-day follow-up. During the study, patients will be visited four times by the investigators. Details of the study procedures are given in Table 3.

**Table 3 Tab3:**
[figure not shown]
Study schedule for patients

*ICF* informed consent form

### Concomitant treatments and forbidden drugs

Patients will be allowed to continue using medications for underlying conditions, such as hypertension or diabetes. The name, dosage, and duration of any concomitant medication must be recorded carefully in the case report form (CRF). If the body temperature of a participant rises to higher than 39.0 °C for longer than 2 hours or becomes ≥39.5 °C, physical cooling and/or paracetamol can be used to kill the fever. During the study period, any other Western or Chinese therapy or medication that may affect the study results is prohibited. Once forbidden drugs are used, the patient will be withdrawn from the study.

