#### Withdrawal criteria

The withdrawal criteria include the following:Worsening conditions during the trial, including no body temperature decline, a rising body temperature higher than 39.0 °C, or worsening symptoms in 48 hoursExperiencing anaphylaxis or serious adverse events during the trialThe study drug is not taken as required, or is taken at doses <80% or >120% of the requirementQuitting the clinical trial voluntarily.

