### Change in TCM symptom and sign scores

The TCM symptom scoring system used in the study follows the *Guidelines for Clinical Research of New Chinese Medicine* [24], in which all symptoms are graded (Table 4). The change in cumulative TCM symptom and sign scores is assessed by the percentage of symptom and sign scores reduction (PSSSR), which is calculated according to the following formula: PSSSR = (scores before treatment – scores after treatment)/scores before treatment*100%. A value greater than 50% is defined as clinically effective.

**Table 4 Tab4:** Symptom and sign scoring system

Symptom	Score			
Primary	None (0)	Mild (2)	Moderate (4)	Severe (6)
Fever	<37.3 °C	37.3–37.9 °C	38.0–38.4 °C	≥38.5 °C, <39.0 °C
Pharynx uncomfortable	–	Dry pharynx	Burning pharynx	Pharynx pain
Secondary	None (0)	Mild (1)	Moderate (2)	Severe (3)
Stuffy nose	–	Heavy sound	Sometimes	Sustained
Running nose	–	Occasionally	Sometimes	Sustained
Thirsty	–	No need for water	Sometimes need water	Need water frequently
Cough	–	Occasionally	Sometimes	Frequently
Headache	–	Occasionally, mild	Sustained, moderate	Heavy, can’t insist on work
Limb pain/soreness	–	Weak, uncomfortable	Painful	Terrible, can’t stretch freely
Cumulative symptom score	Primary symptom scores + secondary symptom scores			
Sign	None (0)	Mild (1)	Moderate (2)	Severe (3)
Pharyngeal hyperemia/swelling	–	Pharyngeal mucosa hyperemia	Pharyngeal mucosa, pharynx palatine arches and uvula hyperemia	Pharyngeal swelling and heavy secretion
Total score	All symptom scores + sign score			

– No symptom

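### A temperature above 39.0 °C meets a withdrawal criterion and also falls under a permitted rescue rule, and the fever scale has no score for it; the rules on serious adverse events also disagree

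*Protocol article*

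**What the plan says.** Four places in the protocol article bear on this.

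- **Withdrawal criteria.** Worsening is described as "including no body temperature decline, a rising body temperature higher than" 39.0 °C, or worsening symptoms, followed by the words for a 48-hour period. The same list names anaphylaxis and serious adverse events.
- **Concomitant treatments and forbidden drugs.** If the temperature "rises to higher than 39.0 °C for longer than 2 hours or becomes ≥39.5 °C", then "physical cooling and/or paracetamol can be used to kill the fever". The section continues that "any other Western or Chinese therapy or medication that may affect the study results is prohibited" and closes with "Once forbidden drugs are used, the patient will be withdrawn from the study".
- **Change in TCM symptom and sign scores, Table 4.** The top fever category, Severe (6), is "≥38.5 °C, <39.0 °C". There is no category above it.
- **Safety evaluation.** After a serious adverse event, "a decision on whether the participant needs to be withdrawn from the study will be made by the principal investigator and ethics committee".

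Three other sections set the context. The exclusion criteria bar a temperature of 39.0 °C or more at entry. Secondary outcomes defines fever relief as a drop of at least 0.5 °C, and fever clearance as below 37.3 °C for 24 hours. Data management and statistical analysis applies last observation carried forward to missing values in the full analysis set.

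**The concern.** Two sections give different instructions for one event. One treats a temperature above 39.0 °C as a reason to leave the study. The other treats it as something to be managed during the study, and the only withdrawal it mentions is for forbidden drugs. With seven centres, either reading can be applied in good faith.

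The choice changes the data. A withdrawn patient is censored in the time-to-event outcomes or has scores carried forward. A patient who stays contributes fever times that cooling or paracetamol may have shortened. Fever relief is defined by temperature alone, so a fall caused by rescue can count as efficacy. These are the patients doing worst, and their handling should not depend on the centre.

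The scale adds a second problem: it cannot score temperatures that the withdrawal and rescue rules both foresee. The serious adverse event rules raise the same question of whether withdrawal is a criterion or a judgement.

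**Working it through.** No stated figure is in dispute. The protocol's sample size reproduces (difference 2 days, SD 3, two-sided α 0.05, power 90%: 48 per group; 48 / (1 − 0.20) = 60) and plays no part here. The check is to pass temperatures through the stated rules.

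| On-study temperature | Withdrawal wording met | Rescue allowed | Table 4 fever score |
|---|---|---|---|
| 38.9 °C | no | no | 6 |
| 39.0 °C | no | no | none |
| 39.1 to 39.4 °C | yes | if longer than 2 hours | none |
| 39.5 °C or more | yes | at once | none |

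Every temperature that allows rescue also meets the withdrawal wording and has no score. No section says which rule takes precedence.

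**The 48-hour words.** They may belong only to worsening symptoms, in which case the table stands as it is. They may instead govern all three items, and then there are further readings:

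- A rise within the first 48 hours: the overlap covers those hours.
- A rise after 48 hours: the overlap still covers 72 − 48 = 24 hours of the 3-day treatment, and follow-up.
- A state that persists over 48 hours: rescue and withdrawal could run in sequence, but the text does not say so.

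The qualifier narrows the overlap and does not remove it.

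**Does a rescued patient stay in?** The prohibition covers any *other* therapy, and withdrawal is attached to forbidden drugs. By implication, permitted rescue does not end participation. This is an inference, though it is the plain reading of the section.

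**The scale.** Entry below 39.0 °C means that every eligible baseline lies below the cap. Scores after treatment need not. The maximum total in Table 4 is 2 × 6 + 6 × 3 + 1 × 3 = 33. Suppose a value at or above 39.0 °C is treated as missing and an earlier fever score of 4 is carried forward in place of 6. The post-treatment total is then 2 points too low, and the percentage reduction is too high by 2 / baseline total, which is at least 2 / 33 = 6.1 percentage points. If the earlier score was already 6, nothing changes.

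**Fever relief.** The reference for the 0.5 °C drop is not stated. A patient who enters at 38.8 °C, rises to 39.4 °C and falls by 0.5 °C is at 38.9 °C. That is no event if the reference is the pre-dose value, and an event if it is the peak.

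**Serious adverse events.** One section lists such an event as a withdrawal criterion. The other provides for a decision on whether withdrawal is needed. If the first is automatic, the second has nothing to decide.

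**The case against.** The strongest reply is that the rules have different purposes: withdrawal concerns failure to improve over 48 hours, and rescue is acute relief after 2 hours. That reading is possible, and on it the conflict shrinks to an ambiguity. The ambiguity still needs a sentence to settle it. It is also true that the section on concomitant treatment never says outright that a rescued patient stays in.

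On the scale, the cap matches the entry limit, a score of 6 is the obvious convention, and the percentage reduction uses scores before and after treatment, not every diary reading. So the gap matters only when a patient is at or above 39.0 °C at a later scoring. That limits the point but does not answer it, because the convention is not written down.

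On serious adverse events, the safety section may simply name who decides. That is a fair reading of half its sentence. No effect on results is shown, and the point is one of consistency.

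Handling of rescue in the analysis is commonly left to the analysis plan, and concomitant medication is recorded, so any strategy remains open. This stands, and the analysis proposal is therefore limited to a sensitivity analysis.

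A reader might infer more than the document supports:

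- *That centres will handle these patients differently.* The text shows only that they can.
- *That each rescued patient becomes a fever-relief event.* The 38.8 °C example shows otherwise if the drop is measured from the pre-dose value, and a patient who had already dropped 0.5 °C before the rise has the event regardless.
- *That any antipyretic fall counts as fever clearance.* Clearance must last 24 hours, which guards against brief falls.
- *That all-symptom clearance after rescue should never count.* One early use of rescue would then make a permanent failure of a patient who recovers days later, which redefines the primary outcome.

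**Conclusion.** The point holds as a conflict between stated rules and a gap in a scale. Every temperature above 39.0 °C that permits rescue also meets the withdrawal wording, subject to what the 48-hour words qualify. No temperature at or above 39.0 °C has a fever score. Withdrawal after a serious adverse event is described in two ways that do not agree.

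The size is unknown. The document gives no frequency of temperatures above 39.0 °C. An assumed 5 to 15% of 60 would be 3 to 9 patients per group, but nothing in the document supports that range and the conclusion does not rest on it. The outcomes exposed are secondary: fever relief, fever clearance and the symptom and sign score. Fever is one of the symptoms in the primary outcome, so rescue could touch that outcome too, but this is no reason to change its definition.

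The conclusion assumes that permitted rescue does not itself end participation, which the section implies without stating. The correction should be made, but the design does not depend on it.

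**What to change.** 1. Reconcile Withdrawal criteria with Concomitant treatments and forbidden drugs for temperatures above 39.0 °C. State what the 48-hour words qualify and whether a patient given permitted rescue remains in the study. The clinical content is for the investigators and sponsor.
2. Reconcile Withdrawal criteria with Safety evaluation on withdrawal after a serious adverse event, likewise leaving the clinical content to them.
3. In Table 4, remove the upper bound of 39.0 °C from the severe fever category so that every on-study temperature at or above 38.5 °C scores 6. No eligible baseline score changes.
4. Add a sensitivity analysis of fever relief and fever clearance in which an event first reached after antipyretic or physical cooling is not counted. Keep the stated definitions for the main analysis and leave the primary outcome as it is.

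The cost is a short clarification sent to all seven centres, one table cell and one additional analysis. Recruitment is under way, so the clarification should be dated and made before unblinding. The drawback of item 4 is that a rescued patient who truly recovers counts as not recovered, which is why it is a sensitivity analysis only.
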